## Abstract

**Background:**

There is still a controversy about the superiority of liposomal bupivacaine (LB) over traditional local anesthetics in postoperative analgesia after thoracic surgery. This study aims to determine the effect of LB versus bupivacaine hydrochloride (HCl) for preoperative ultrasound-guided erector spinae plane block (ESPB) on postoperative acute and chronic pain in patients undergoing video-assisted thoracoscopic lung surgery.

**Methods:**

This multicenter, randomized, double-blind, controlled trial will include 272 adult patients scheduled for elective video-assisted thoracoscopic lung surgery. Patients will be randomly assigned, 1:1 and stratified by site, to the liposomal bupivacaine (LB) group or the bupivacaine (BUPI) HCl group. All patients will receive ultrasound-guided ESPB with either LB or bupivacaine HCl before surgery and patient-controlled intravenous analgesia (PCIA) as rescue analgesia after surgery. The numeric rating scale (NRS) score will be assessed after surgery. The primary outcome is the area under the curve of pain scores at rest for 0–72 h postoperatively. The secondary outcomes include the total amount of opioid rescue analgesics through 0–72 h postoperatively, time to the first press on the PCIA device as rescue analgesia, the area under the curve of pain scores on activity for 0–72 h postoperatively, NRS scores at rest and on activity at different time points during the 0–72 h postoperative period, Quality of Recovery 15 scores at 72 h after surgery, and NRS scores on activity on postsurgical day 14 and postsurgical 3 months. Adverse events after the surgery are followed up to the postsurgical day 7, including postoperative nausea and vomiting, fever, constipation, dizziness, headache, insomnia, itching, prolonged chest tube leakage, new-onset atrial fibrillation, severe ventricular arrhythmia, deep venous thrombosis, pulmonary embolism, pulmonary atelectasis, cardiac arrest, ileus, urinary retention, chylothorax, pneumothorax, and organ failure. Analyzes will be performed first according to the intention to treat principle and second with the per-protocol analysis.

**Discussion:**

We hypothesize that LB for preoperative ultrasound-guided ESPB would be more effective than bupivacaine HCl in reducing postoperative pain in video-assisted thoracoscopic lung surgery. Our results will contribute to the optimization of postoperative analgesia regimens for patients undergoing video-assisted thoracoscopic lung surgery.

**Clinical trial registration****:**http://www.chictr.org.cn, identifier ChiCTR2300074852.

## Introduction

Thoracoscopic surgery has emerged as the backbone of surgical procedures for lung resection in recent years, but these procedures still cause moderate-to-severe postoperative acute and chronic pain (1–4). Preemptive analgesia is regarded as a proven approach to minimize postsurgical pain (5). Several preemptive analgesia approaches have been employed in thoracoscopic surgery, including paravertebral block, intercostal nerve block, and thoracic epidural block (6). The erector spinae plane block (ESPB), a new inter-fascial plane block technique first described in 2016 for thoracic pain treatment (7), has the advantages of easy handling, high safety, and a good analgesic effect (8, 9). However, ESPB with a single dosage of currently available local anesthetics is limited by the short duration of analgesia (typically 24 h or less). The duration of analgesia can be prolonged by continuous peripheral nerve blocks using a perineural catheter; however, this may result in a variety of inconveniences and side effects, such as management complexity, catheter-related infections, leakage, and accidental dislocation (10, 11).

Liposome bupivacaine (LB) is a novel local anesthetic with water-soluble bupivacaine wrapped in a liposome, allowing for a steady, continuous release of the drug for up to 72 to 96 h (12, 13). In 2011, liposomal bupivacaine was approved by the U.S. Food and Drug Administration to be used in single-dose wound infiltration for postsurgical analgesia in adults, and then the indication was expanded to transverse abdominis plane blocks and interscalene brachial plexus blocks (14, 15). Liposome bupivacaine appears safe when used in fascial plane blocks and peripheral nerve blocks (16–20). Whether LB is superior to traditional local anesthetics in postoperative analgesia after thoracic surgery remains controversial. Several retrospective studies have suggested that LB applied in minimally thoracic surgery improved postoperative pain, decreased opioid use, and shortened hospital stay in comparison with bupivacaine hydrochloride (HCl) (21–23). A recent randomized controlled trial including 50 patients undergoing minimally invasive lung surgery indicated that LB for intercostal nerve block provided no benefit in mitigating postoperative pain compared with bupivacaine plus epinephrine (18). However, that study had a smaller sample size and did not exclude the patients with more complex pain problems. To date, the analgesic efficacy of LB used in ESPB procedures on acute or chronic postsurgical pain remains unknown.

In this context, we designed this multicenter randomized controlled trial to determine the effect of LB versus bupivacaine HCl for preoperative ultrasound-guided ESPB on postoperative acute and chronic pain in patients undergoing video-assisted thoracoscopic lung surgery. In addition, we will also evaluate its safety profile when used in the ESPB procedures.

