**Figure 1 fig1:**
[figure not shown]
Study flow diagram.

**Table 1 tab1:** Diagrammatic representation of trial processes.

	Pre-Op (study days-6-0)	Allocation 2 h before surgery	Intra-Op (study day 1)	PACU (study day 1)	Post-Op (0–72 h) (study days 1–4)	Day of discharge	Post-Op (study days 5–8)	Post-Op (study day 15)	Post-Op 3 months
Enrollment									
Eligibility screening	╳								
Informed Consent	╳								
Demographics	╳								
Randomization		╳							
Allocation		╳							
Vital signs			╳						
Interventions									
ESPB procedure			╳						
Measurements									
Intra-operative information			╳						
NRS scoring at rest				╳	╳				
NRS scoring on activity				╳	╳			╳	╳
Opioid rescue medication					╳	╳			
Initiation of postoperative activities					╳				
QoR-15 scores					╳				
Chest tube evaluation					╳	╳	╳ (If applicable)		
Adverse events^a^			╳	╳	╳	╳	╳		
Oral analgesic medication					╳	╳	╳ (If applicable)	╳ (If applicable)	╳ (If applicable)

According to the SPIRIT statement of defining a standard protocol for clinical trials. Op, Operation; ESPB, erector spinae plane block; NRS, numeric rating scale; QoR-15 scores, Quality of Recovery 15 scores.

a including postoperative nausea and vomiting, fever, constipation, dizziness, headache, insomnia, itching, prolonged chest tube leakage, new-onset atrial fibrillation, severe ventricular arrhythmia, deep venous thrombosis, pulmonary embolism, pulmonary atelectasis, cardiac arrest, ileus, urinary retention, chylothorax, pneumothorax, and organ failure.

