### Participants and enrollment

We plan to recruit eligible subjects who meet the following inclusion criteria: (1) American Society of Anesthesiologists (ASA) class I-III, (2) adult subjects who are 18–75 years of age, and (3) subjects scheduled for elective video-assisted thoracoscopic single or multi-port lung surgery under general anesthesia with bronchial intubation.

The exclusion criteria are as follows: (1) trauma and emergency subjects, (2) subjects with New York Heart Function Scale (NYHA) levels of 3–4, (3) patients with heart conduction block (sinus block or atrioventricular block), (4) patients with unstable coronary artery disease, (5) patients with gastric ulcer or gastric bleeding, (6) patients with body mass index (BMI) of <18 kg/m^2^ or > 37 kg/m^2^, (7) patients with diabetes and are being treated with insulin, (8) patients with renal dysfunction (serum creatinine values exceed normal thresholds), (9) patients with liver dysfunction (Alanine aminotransferase or Aspartate aminotransferase is more than twice the normal value), (10) subjects with coagulation dysfunction (prothrombin time or activated partial thromboplastin time is higher than the normal threshold) or patients who are taking oral anticoagulants for other medical reasons and have not stopped it before surgery, such as warfarin or new anticoagulants rivaroxaban or dabigatran, (11) subjects with alcohol abuse or heavy dependence on narcotic drugs in the last 2 months, (12) subjects with uncontrolled anxiety, schizophrenia, or other mental illness, (13) subjects who are pregnant or preparing for pregnancy, and (14) subjects with a history of allergy to local anesthetic drugs or any of the experimental medications. Written informed consent will be signed by participants before enrollment.

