### Perioperative management

The flow of the participants through this trial is depicted in Figure 1. Subjects do not receive sedative or analgesic medications preoperatively. In the operating room, standard monitoring includes electrocardiography, non-invasive cuff blood pressure, pulse oximetry, and temperature. The left or right radial artery is cannulated following anesthesia induction, and continuous radial artery pressure is measured. General anesthesia is induced with propofol (2–2.5 mg/kg), sufentanil (0.3–0.5 μg/kg), and cisatracurium (0.2 mg/kg) in sequence. Following tracheal intubation with a double-lumen tube, unilateral bronchial ventilation is conducted with a tidal volume of 4–6 mL/kg and a respiratory rate of 12–16 times/min, aiming to maintain the end-tidal carbon dioxide at 35–45 mmHg and pulse oxygen saturation of ≥95%. The location of the bronchial tube is then confirmed using flexible fiberoptic bronchoscopy. Anesthesia is maintained with sevoflurane inhalation targeting a bispectral index value between 40 and 60. Intraoperative analgesia is provided with sufentanil and remifentanil: sufentanil 0.1–0.2 μg/kg is given before incision at the beginning of surgery, and remifentanil (0.05–0.2 μg/kg/min) is infused continuously for intra-operative analgesia. Additional doses of sufentanil can be given intraoperatively if necessary, and sufentanil is added 0.1–0.2 μg/kg when the remifentanil is discontinued at the end of the operation. The additional doses of cisatracurium can be incremented intraoperatively as needed. Intraoperative hypotension (defined as a decrease in mean blood pressure [MBP] of >20% of baseline or MBP of <65 mmHg) would be treated with intravenous ephedrine of 6–10 mg or phenylephrine of 50–100 μg, and bradycardia (defined as heart rate [HR] of <50 beats/min) would be treated with intravenous atropine of 0.3–0.5 mg.

At the end of the surgery, all subjects received ondansetron of 8 mg as an antiemetic after the last stitches. Subjects are transferred to a post-anesthesia care unit (PACU) and kept there for at least 1 h before returning to the thoracic ward. The surgical day is regarded as the study day 1, and the day following surgical day is the study day 2.

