#### Secondary outcomes

The secondary outcomes include (1) the total amount of opioid rescue analgesics through 0–72 h postoperatively, (2) the time to first press on the PCIA device as rescue analgesia, (3) the area under the curve of pain scores on activity for 0–72 h (AUC NRS-A_0-72_) postoperatively, (4) NRS scores at rest and on the activity at different time points during the 0–72 h postoperative period, (5) Quality of Recovery 15 (QoR-15) scores at 72 h after surgery, (6) NRS scores on activity on postsurgical day 14 (study day 15), which will be followed up via telephone, with a permitted time window of 14 ± 3 days, and (7) NRS scores on the activity at postsurgical 3 months will be followed up via telephone, with a permitted time window of 3 months ±7 days. Opioids are first converted to intravenous morphine equivalents for each subject, and then the total amount will be naturally logarithmically converted before analysis. The time to first opioid rescue analgesia using PCIA was measured in hours, i.e., the date and time of the first opioid rescue minus the date and time of the end of surgery.

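### Chronic postoperative pain is part of the aim, but pre-existing pain is neither excluded nor recorded, so the 3-month NRS cannot be read as chronic postsurgical pain

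*Protocol article*

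**What the plan says.** **Rationale and aim.** The Introduction describes a 50-patient randomized trial that found no benefit of LB for intercostal block, and comments that it was smaller and "did not exclude the patients with more complex pain problems". The present trial is then introduced as a study of the effect of LB versus bupivacaine HCl "on postoperative acute and chronic pain in patients undergoing video-assisted thoracoscopic lung surgery. In addition, we will also evaluate its safety profile".

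**Eligibility.** *Participants and enrollment* lists three inclusion and 14 exclusion criteria. The two exclusions nearest to complex pain are "subjects with alcohol abuse or heavy dependence on narcotic drugs in the last 2 months" and "subjects with uncontrolled anxiety, schizophrenia, or other mental illness".

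**Pre-operative analgesics.** *Perioperative management* adds: "Subjects do not receive sedative or analgesic medications preoperatively".

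**Timing of pain scores.** In Table 1 the row "NRS scoring on activity" is marked for the PACU, 0–72 h, study day 15 and 3 months. The row for pain at rest is marked for the PACU and 0–72 h. Neither is marked in the pre-operative column. *Postsurgical assessments* puts the first score about 15 minutes after extubation.

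**The 3-month outcome.** The seventh secondary outcome reads: "NRS scores on the activity at postsurgical 3 months will be followed up via telephone". The window is 7 days either side. No body site, time of onset or comparison with the state before surgery is given.

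**The concern.** The protocol explains away a null result by a weakness in patient selection, then does not clearly remove that weakness from its own selection. On its own this would be a matter of rationale. It matters more because chronic postoperative pain is in the stated aim, and the one score that addresses it directly can contain pain that has nothing to do with the operation.

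Take a hypothetical patient who had shoulder pain on movement of 5 before surgery and has no chest pain at 3 months. Asked for pain on activity, this patient may answer 5, and that value enters the mean of the arm. Nothing scheduled in the article would allow it to be recognised later. At stake are the precision of the 3-month comparison and what may be said about its result.

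**Working it through.** The plan states no figure on this point. The sample size concerns resting pain over 0–72 h and is not affected. The check is therefore a comparison of sections, followed by a short derivation of what unrecorded prior pain does to the comparison.

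**1. Is there a pain-related exclusion?** By subject, the 14 criteria are: trauma or emergency (1); cardiac (2–4); gastric (5); body mass index (6); insulin-treated diabetes (7); renal, hepatic and coagulation (8–10); alcohol or narcotics (11); mental illness (12); pregnancy (13); allergy (14). None names chronic pain, earlier chest pain or regular analgesic use. Criteria 11 and 12 will remove some patients with complex pain. They will not remove, for example, a patient with long-standing back pain who takes a non-opioid.

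**2. Does the rule on pre-operative analgesics fill the gap?** No. It stands under perioperative management, describes what is given before the operation, and neither selects patients nor measures pain.

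**3. Is pain recorded before surgery?** Table 1 and *Postsurgical assessments* agree that scoring begins after extubation.

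**4. Is the 3-month score tied to the operation?** *Secondary outcomes* names no site. *Postsurgical assessments* describes pain on activity as pain on turning in bed or on active movement, again without a site.

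**5. Effect on the comparison.** Write a patient's 3-month score as Y = S + bX, where

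- S is pain due to the operation,
- X is 1 if the patient has persisting pain from before surgery (probability p) and 0 otherwise,
- b is the number of points that this pain adds.

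Randomization makes p the same in both arms in expectation, so

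E(Y, LB) − E(Y, BUPI) = [E(S, LB) − E(S, BUPI)] + b(p − p) = E(S, LB) − E(S, BUPI).

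The expected difference is unchanged. If S and X are independent,

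Var(Y) = Var(S) + b²p(1 − p),

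and with n patients per arm and the same Var(S) in both, the standard error of the difference is √(2[Var(S) + b²p(1 − p)]/n). The price is the term b²p(1 − p). Chance imbalance in X between the arms is what this term describes, so it is already inside the standard error.

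**6. Effect on interpretation.** Within an arm, E(Y) = E(S) + bp. With X not recorded, bp cannot be separated from E(S), so the level of the score is not a level of chronic postsurgical pain.

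**7. Can a number be given?** No. The documents give none of p, b and Var(S) at 3 months.

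**The case against.** **The comparison is randomized and the outcome is defined as a score.** This stands. The protocol sets no case definition or threshold for chronic pain, and the difference in mean NRS is unbiased. A reader might infer that prior pain biases the result or dilutes the effect. With an additive contribution it does neither. Attenuation would need other pain to mask chest pain, and the documents say nothing on that.

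**Chance imbalance might be turned into a shift in NRS points.** A reader might assume a prevalence and a number of points, take the 95% extreme of the imbalance, and compare it with the primary target of 15 over 72 h (15/72 = 0.21 point). The documents do not support this. The extreme is ordinary sampling error that the confidence interval already covers, the target belongs to resting pain over 72 h, and both inputs would be invented.

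**The criticism of the earlier trial is answered in part.** Its size is addressed (272 patients against 50). The phrase about complex pain problems is not defined, and two exclusions touch on it. So the contradiction is partial, and the Introduction does not promise a chronic-pain exclusion.

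**An article condenses.** Table 1 is not complete: daily scores up to study day 15 are described in the text but not marked in the column for study days 5–8. Baseline characteristics are mentioned in *Statistical analysis* without a list, and the wording of the telephone question may stand in the case report form. This lowers the certainty. It does not remove the point, because the eligibility list is numbered, the start of pain scoring is stated in two places, and no analysis plan can adjust for a baseline that was not collected.

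**A baseline covariate for acute pain is a preference.** Agreed. No correlation between pre-operative and postoperative pain is given, so no gain can be shown.

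**Conclusion.** The point holds as one of measurement and interpretation. As published, the plan has no pain-related exclusion, no pre-operative pain score, and a 3-month score tied neither to the operated chest nor to onset after surgery. The LB versus BUPI contrast at 3 months stays unbiased. The harm is added variance, of a size that the documents do not allow one to compute, and a score that cannot be interpreted as chronic postsurgical pain.

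The outcome is the last of seven secondary outcomes. The primary comparison remains valid, so the matter deserves a small amendment and does not threaten the trial. The conclusion assumes that the unpublished case report form does not already collect pre-operative pain or name the surgical site. If it does, only the description in the article needs correcting.

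**What to change.** 1. **Patients still to be enrolled:** add NRS at rest and on activity to the pre-operative column of Table 1, with yes/no items on chronic pain and on regular analgesic use.
2. **The 3-month call:** ask whether the pain is at the surgical site and whether it was present before surgery. This also serves patients already enrolled but not yet called.
3. **Reporting:** keep the raw NRS as the stated secondary outcome, and show beside it the result for surgical-site pain that is new or worse than before surgery. Add a supportive analysis adjusted for baseline NRS where a baseline exists.
4. **Wording:** where these data are not available, report the result as pain on activity at 3 months, not as chronic postsurgical pain.

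The cost is an amendment, a few short questions at an existing screening visit and two in an existing call. No visit or procedure is added and no treatment changes. The downside is that recruitment had already begun when the article was submitted (*Study design and status*), so baseline pain will be missing or recalled for patients already enrolled. The adjusted and new-or-worse analyses can therefore only be supportive.

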## Methods

### Ethics and registration

The study protocol was approved by the ethics committees of the leading center (the First Affiliated Hospital of Soochow University, Suzhou; Approval No. 2023–207) and each participating center. This trial was registered at the Chinese Clinical Trial Registry (http://www.chictr.org.cn, identifier: ChiCTR2300074852) before the enrollment of the first subject. This protocol adheres to the guidelines of Standard Protocol Items: Recommendations for Interventional Trials (SPIRIT) statement (24).

### Study design and status

This investigator-initiated, multicenter, randomized, double-blind, parallel-controlled trial will be conducted at 12 tertiary hospitals in China. Subjects will be randomized to receive either liposomal bupivacaine or bupivacaine HCl for ultrasound-guided ESPB after induction of anesthesia. Group allocation is performed by the online central randomization system.

This trial start date is 1 September 2023, and the anticipated end date is 31 March 2025. By the time of this manuscript submission, the recruitment of participants has started, but all follow-up data will be stored in the electronic data capture (EDC) system, which will be locked until the final analysis. Figure 1 shows the study flow diagram. Table 1 presents the schedule of subject enrollment, study intervention, and outcome evaluation following the SPIRIT statement.

**Figure 1 fig1:**
[figure not shown]
Study flow diagram.

**Table 1 tab1:** Diagrammatic representation of trial processes.

	Pre-Op (study days-6-0)	Allocation 2 h before surgery	Intra-Op (study day 1)	PACU (study day 1)	Post-Op (0–72 h) (study days 1–4)	Day of discharge	Post-Op (study days 5–8)	Post-Op (study day 15)	Post-Op 3 months
Enrollment									
Eligibility screening	╳								
Informed Consent	╳								
Demographics	╳								
Randomization		╳							
Allocation		╳							
Vital signs			╳						
Interventions									
ESPB procedure			╳						
Measurements									
Intra-operative information			╳						
NRS scoring at rest				╳	╳				
NRS scoring on activity				╳	╳			╳	╳
Opioid rescue medication					╳	╳			
Initiation of postoperative activities					╳				
QoR-15 scores					╳				
Chest tube evaluation					╳	╳	╳ (If applicable)		
Adverse events^a^			╳	╳	╳	╳	╳		
Oral analgesic medication					╳	╳	╳ (If applicable)	╳ (If applicable)	╳ (If applicable)

According to the SPIRIT statement of defining a standard protocol for clinical trials. Op, Operation; ESPB, erector spinae plane block; NRS, numeric rating scale; QoR-15 scores, Quality of Recovery 15 scores.

a including postoperative nausea and vomiting, fever, constipation, dizziness, headache, insomnia, itching, prolonged chest tube leakage, new-onset atrial fibrillation, severe ventricular arrhythmia, deep venous thrombosis, pulmonary embolism, pulmonary atelectasis, cardiac arrest, ileus, urinary retention, chylothorax, pneumothorax, and organ failure.

